## **General Information**

This protocol describes the NMES clinical trial, and provides information about the procedures for entering patients into the trial. The protocol should not be used as a guide, or as an aide-memoire for the treatment of other patients. Every care has been taken in drafting this protocol; however, corrections or amendments may be necessary. These will be circulated to the known investigators in the trial, but centres entering patients for the first time are advised to contact the Wales Cancer Trials Unit in Cardiff to confirm that they have the most up-to-date version of the protocol in their possession. Problems relating to the trial should be referred, in the first instance, to the Wales Cancer Trials Unit.

## **Compliance**

This trial will adhere to the conditions and principles which apply to all clinical trials as outlined in the ICH Harmonised Tripartite Guideline for Good Clinical Practice (CPMP/ICH/135/95). It will be conducted in compliance with the protocol; the Research Governance Framework for Health and Social Care (Welsh Assembly Government November 2001 and Department of Health 2nd July 2005); the Data Protection Act 1998 and other regulatory requirements as appropriate.

## **Funding**

The NMES trial is being funded by the National Cancer Research Institute Supportive and Palliative Care Lung Cancer Initiative, on behalf of the National Cancer Research Institute and thus is part of the NCRN portfolio of clinical trials.

## **Abbreviations and glossary**

|                    |                                                                                                                                  |
|--------------------|----------------------------------------------------------------------------------------------------------------------------------|
| AE          | Adverse Event                                                                                                                    |
| CI          | Chief Investigator                                                                                                               |
| COPD        | Coronary Obstructive Pulmonary Disease                                                                                           |
| CRF         | Case report form                                                                                                                 |
| CTCAE       | Common Terminology Criteria for Adverse Events                                                                                   |
| DEXA        | Dual Energy X-ray Absorptiometry                                                                                                 |
| ECOG        | Eastern Cooperative Oncology Group                                                                                               |
| GCP         | Good Clinical Practice                                                                                                           |
| GP          | General practitioner                                                                                                             |
| ICH         | International Conference on Harmonisation                                                                                        |
| ICH-GCP     | International Conference on Harmonisation – Good Clinical Practice                                                               |
| IDMC        | Independent Data Monitoring Committee                                                                                            |
| ISF         | Investigator Site File                                                                                                           |
| ISRCTN      | International Standard Randomised Controlled Trial Number                                                                        |
| LREC        | Local Research Ethics Committee                                                                                                  |
| MHRA        | Medicines and Healthcare products Regulatory Agency                                                                              |
| NCRI        | National Cancer Research Institute                                                                                               |
| NCRN        | National Cancer Research Network                                                                                                 |
| NHS         | National Health Service                                                                                                          |
| NMES        | Neuromuscular electrical stimulation                                                                                             |
| NSCLC       | Non-small cell lung cancer                                                                                                       |
| Patient     | A patient under care who may be eligible for the trial but has not yet consented to participate in any trial related activities. |
| Participant | An individual who has given written informed consent and is participating in trial related activities                            |
| PI          | Principal Investigator                                                                                                           |
| PIS         | Participant Information Sheet                                                                                                    |
| R&D     | Research and Development                                                                                                         |
| REC         | Research Ethics Committee                                                                                                        |
| SAE         | Serious Adverse Event                                                                                                            |
| SOP         | Standard Operating Procedure                                                                                                     |
| SSA         | Site-specific assessment                                                                                                         |

|              |                                                |
|--------------|------------------------------------------------|
| TMF   | Trial Master File                              |
| TMG   | Trial Management Group                         |
| TSC   | Trial Steering Committee                       |
| TSF   | Trial Site File                                |
| UKCRC | United Kingdom Clinical Research Collaboration |
| WCTU  | Wales Cancer Trials Unit                       |

## 1.0 Trial schema

[figure not shown]

### Primary outcome measure:

- *Adherence to NMES*: self-report daily diary of length of time NMES used and internal logger recording total and individual periods of use.

### Secondary outcome measures:

- *Safety of NMES*: toxicities will be assessed according to the NCI Common Terminology Criteria for Adverse Events (NCI CTCAE v3.0). Serious adverse events will be monitored in "real-time".
- *Quadriceps muscle strength*: peak torque (kg) measured using a portable Manual Muscle Tester dynamometer (Lafayette Instruments, USA).
- *Body composition*: lean tissue mass of the body and thighs (kg) assessed by low-dose dual energy x-ray absorptiometry (DEXA).
- *Physical activity level*: mean daily step count assessed by a small, lightweight activPAL™ accelerometer worn on the thigh for one week.
- *Nutritional intake*: mean daily energy (kJ/d) and protein (g/d) intake estimated from a 3-day food and drink diary.
- *Fatigue*: Multidimensional Fatigue Inventory.
- *Quality of life*: the EORTC-C30 and the lung cancer specific module LC-13.
- *Experience of NMES* - semi-structured interview exploring patient experiences of completing NMES during chemotherapy.

## 2.0 Trial synopsis

|                             |                                                                                                                                                                       |              |    |              |  |   |
|-----------------------------|-----------------------------------------------------------------------------------------------------------------------------------------------------------------------|--------------|----|--------------|--|---|
| Study title:         | Is neuromuscular electrical stimulation an acceptable and feasible supportive therapy for patients with non-small cell lung cancer receiving palliative chemotherapy? |              |    |              |  |   |
| Study acronym:       | NMES                                                                                                                                                                  |              |    |              |  |   |
| Short title:         | NMES for patients with NSCLC receiving palliative chemotherapy                                                                                                        |              |    |              |  |   |
| ISRCTN No:           | 42944026                                                                                                                                                              |              |    |              |  |   |
| Funder:              | National Cancer Research Institute                                                                                                                                    | Funder's No: |    | LCSuPaC 35   |  |   |
| Chief Investigator:  | [name]                                                                                                                                                     |              |    |              |  |   |
| Sponsor:             | Nottingham University                                                                                                                                                 |              |    |              |  |   |
| Study period:        | 2 years                                                                                                                                                               | Phase:       | II | No. of arms: |  | 2 |
| No. of participants: | 47                                                                                                                                                                    |              |    |              |  |   |

### **Objectives**

**Primary:** Is NMES an acceptable and feasible supportive therapy for patients with non-small cell lung cancer undergoing at least 3 cycles of palliative chemotherapy?

### **Secondary:**

- i) Is NMES a safe intervention to offer patients undergoing palliative chemotherapy?
- ii) To what extent does 3 cycles of palliative chemotherapy impact on leg muscle strength, body composition and physical activity levels in patients with NSCLC and can the use of NMES influence these changes?
- iii) What is the rate of recovery or decline in these parameters following cessation of 3–4 cycles of chemotherapy and can the use of NMES influence this?
- iv) What are patients' attitudes about the use of NMES during chemotherapy?

### **Main inclusion criteria:**

- Equal or greater than 16 years of age
- Histological diagnosis of non small cell lung cancer
- ECOG performance status of 0, 1 or 2
- Scheduled to receive 3–4 cycles of first line palliative chemotherapy
- Able to use the NMES device
- Able to provide written informed consent to participate in trial.

### **Main exclusion criteria:**

- Implanted cardiac pacemaker
- Epilepsy
- Spinal cord pathology
- Pregnancy

**Treatments:****Control arm**

3–4 cycles of first line palliative chemotherapy administered as part of usual care.

**NMES arm**

3–4 cycles of first line palliative chemotherapy with carboplatin/vinorelbine administered as part of usual care plus NMES for 30min daily at home to the anterior thighs throughout chemotherapy.

**Trial assessments:****Baseline assessments:**

Quadriceps muscle strength  
Body composition  
Physical activity level  
Nutritional intake  
Fatigue  
Quality of life

**Ongoing assessments during NMES programme:**

Adherence to NMES  
Safety of NMES

**9 weeks from start of chemotherapy assessments:**

Quadriceps muscle strength  
Body composition  
Physical activity level  
Nutritional intake  
Fatigue  
Quality of life  
Experience of NMES

**12 weeks from start of chemotherapy assessments (if cycle 4 received):**

Experience of NMES

**17/20 week from start of chemotherapy assessments (3/4 cycles received)**

Quadriceps muscle strength  
Body composition  
Physical activity level  
Nutritional intake  
Fatigue  
Quality of life

**Endpoints:****Primary outcome measure:**

- *Adherence to NMES:* Proportion of patients completing a pre-determined level of compliance to the recommended NMES programme measured using a self-report diary.

**Secondary outcome measures:**

- Safety of NMES: toxicities will be assessed according to the NCI Common Terminology Criteria for Adverse Events (NCI CTCAE v3.0). Serious adverse events will be monitored in "real-time".
- Quadriceps muscle strength: peak torque (Nm) measured using a portable Manual Muscle Tester dynamometer (Lafayette Instruments, USA).
- Body composition: lean tissue mass of the body and thighs (kg) assessed by low-dose dual energy x-ray absorptiometry (DEXA).

- Physical activity level: mean daily step count assessed by an activPAL™ monitor over 1 week.
- Nutritional intake: mean daily energy (kJ/d) and protein (g/d) intake estimated from a 3-day (2 weekdays, 1 weekend day) food and drink diary.
- Fatigue: Multidimensional Fatigue Inventory.
- Quality of life: the EORTC-C30 and LC-13.
- Experience of NMES - qualitative sub-study. A semi-structured interview exploring patients experiences of completing NMES during chemotherapy.

## 2.1 Lay summary

People with lung cancer receive chemotherapy to improve symptoms and survival. However, chemotherapy can make leg muscles weak. The reason is unclear, but may relate to reduced activity due to fatigue. Maintaining leg muscle strength is important as this helps determine how active and independent a person is.

Exercise helps maintain leg muscle strength, but even simple forms, e.g. walking, can be difficult when fatigued. An alternative form of exercise is the use of neuromuscular electrical stimulation (NMES). A small battery operated stimulator with two pads placed over each thigh produces a controlled, comfortable, slow contraction and relaxation of the underlying muscles while the person is seated. Our group recently found that NMES 30min daily for one month improved leg muscle strength and physical activity levels in people with lung cancer not on chemotherapy.

NMES looks a promising therapy. However, to determine if NMES is worth pursuing, we wish to examine if it is acceptable to a larger group of people. Given that chemotherapy weakens leg muscles, it is also appropriate that we examine its use in this setting. We would also like to explore further why chemotherapy causes leg muscle weakness.

47 people due to receive chemotherapy will be required for the study. One third will be randomised to receive usual care and two thirds to receive usual care plus NMES. The NMES group will be asked to use the treatment on both legs daily throughout their 3–4 cycles of chemotherapy. Acceptability of NMES will be assessed by diary records of how much the stimulator is used. The potential benefit of NMES will be explored by assessing leg muscle strength, muscle size and physical activity levels, and asking people about their experiences. We will also explore why leg muscles become weaker during chemotherapy by assessing fatigue and nutritional factors and documenting the response of the cancer to chemotherapy. The intervention will be monitored for safety in real time.

### 3.0 Background, rationale and objectives

Palliative chemotherapy is offered to patients with non-small cell lung cancer (NSCLC) to improve symptoms, quality of life and survival. However, not all patients benefit and chemotherapy, contrary to the above aim, can lead to a deterioration in leg muscle strength and physical activity levels. The reason is unclear, but may relate to fatigue causing reduced activity and muscle deconditioning. In order to help patients remain as independent as possible, new approaches are required to help minimise this negative effect of chemotherapy.

One option is exercise. However, in patients with incurable cancer, traditional forms of exercise are limited by low rates of uptake and adherence. Alternative forms of exercise are needed which require less motivation and change in lifestyle. One approach is neuromuscular electrical stimulation (NMES). A small battery operated stimulator with two skin electrodes placed over each thigh produces a controlled, comfortable, slow contraction and relaxation of the underlying muscles while the person is seated. This has improved muscle strength and exercise capacity in patients with COPD and heart failure.

The Nottingham group has just completed a pilot study of NMES in patients with incurable NSCLC not receiving chemotherapy (n=16). Patients were randomised to undertake NMES to each thigh for 30min daily for one month or to a control group which received usual care. NMES appeared acceptable and was used for a median (range) of 80% (69–100) of the total recommended time. Change from baseline in leg muscle strength, physical activity (daily step count) and exercise endurance (endurance shuttle walk test) revealed a trend towards benefit from NMES.

Thus, NMES appears worthy of further examination as a supportive therapy for cancer-related cachexia. However, because chemotherapy also weakens leg muscles, it is appropriate that we explore the potential benefit of NMES in this setting before embarking on a phase III trial. We will also explore why leg muscles become weaker during chemotherapy by assessing fatigue and nutritional factors and documenting the response of the cancer to chemotherapy.

#### Overall aim

To provide data which will help determine the feasibility and justification for a phase III trial of NMES.

#### Primary objective

Is NMES an acceptable and feasible supportive therapy for patients with non-small cell lung cancer undergoing at least 3 cycles of palliative chemotherapy?

#### Secondary objectives

- i) Is NMES a safe intervention to offer patients undergoing palliative chemotherapy?
- ii) To what extent does 3-4 cycles of palliative chemotherapy impact on leg muscle strength, body composition and physical activity levels in patients with NSCLC and can the use of NMES influence these changes?
- iii) What is the rate of recovery or decline in these parameters following cessation of 3–4 cycles of chemotherapy and can the use of NMES influence this?
- iv) What are patients' attitudes to the use of NMES during chemotherapy?

## 4.0 Study design

An open randomised phase II study in patients with non-small cell lung cancer. 47 patients will be randomised to receive either palliative chemotherapy or palliative chemotherapy plus the NMES programme. Patients will be randomised with a 2:1 allocation ratio in favour of the NMES intervention arm.

A Fleming's one-stage design is applied to the experimental arm, with the proportion of patients completing NMES for 30 minutes, three times a week as the primary endpoint.

A control arm will be used to see what the change in activity is (muscle strength, body composition, physical activity, safety) in a similar population of patients having usual practice of palliative chemotherapy.

## 5.0 Participating centre selection

This study will be carried out at the City Hospital Campus of Nottingham University NHS Trust.

The following documentation must be received by the WCTU in order for this centre to begin recruitment:

- Confirmation of local research ethics committee (LREC) approval (Site-specific assessment)
- Confirmation of local R&D approval
- Documentation of delegated responsibilities to PI at site
- Current Curriculum Vitae of the PI
- A copy of the most recent version of the Participant Information Sheet and Consent Form on host care organisation headed paper
- Completed Investigator Statement (signed and dated by the PI)
- Completed Delegation Log (signature list and delegation of responsibilities)
- Full contact details for all host care organisation personnel, indicating preferred contact
- Written confirmation that the PI will ensure that participants are competent to administer the trial treatment

Once all the documentation has been received at the WCTU, confirmation of centre approval will be sent by the WCTU to the centre PI.

All documentation must be stored in the Investigator Site File (ISF) at the site and in the Trial Site File (TSF) at the WCTU. The WCTU must be notified of any changes to the trial personnel and their responsibilities during the running of the trial and the respective trial files must contain this up-to-date information.

## 6.0 Participant eligibility

A total of 47 participants are required for the NMES trial.

Any queries about whether a patient is eligible to enter the trial should be discussed with the WCTU before randomisation. Concerns will then be raised with the Chief Investigator (CI) or one of the clinical Co-Investigators in the CI's absence.

Patients are eligible for the trial if all the inclusion criteria (Section 6.1) are met and none of the exclusion criteria (Section 6.2) apply:

### 6.1 Inclusion criteria

Patients meeting all of the following criteria may be included in the trial:

- Aged 16 years or older
- ECOG Performance Status score of 0, 1 or 2
- Is scheduled to receive 3–4 cycles of first line palliative chemotherapy
- Able to use NMES device
- Life expectancy > 3 months
- Has provided written informed consent.

The researcher must confirm the eligibility of a patient in the patient's medical notes prior to randomisation.

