### 9.5 Follow up assessments (17 / 20 weeks from start of chemotherapy)

- Quadriceps muscle strength
- Toxicities
- Body composition
- Physical activity level
- Nutritional intake
- Fatigue
- Quality of life.

A detailed assessment schedule is given in section 9.6 overleaf.

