### 12.3 Sample size calculation

This trial is powered as a Fleming's single stage phase II trial of the intervention arm. The main endpoint is the proportion of patients completing a pre-determined level of compliance to the recommended NMES programme (NMES for 30min three times a week) measured using a self-report daily diary. Following advice from the cachexia subgroup of the NCRI Palliative Care Clinical Studies Group we have determined that 80% of patients should adhere to this minimum level in order to warrant a future phase III study. Conversely, if  $\leq 50\%$  adhered to this minimum level, this would give grounds to reject further study. Using a Fleming's one stage method, 20 patients will be required to distinguish between these rates (90% power,  $p=0.05$ ) and if  $\geq 15$  out of 20 patients adhere, this would warrant further investigation.

We have included a randomised control arm into this trial design in order to allow comparison of some secondary end points. Originally the trial started by randomising with a 1:1 allocation; however this was changed to a 2:1 in favour of the NMES arm allocation part way through the trial in order to support recruitment. As the study analysis is based on a within-intervention arm analysis, the statistical integrity of the study is not affected. A local audit suggests about 25% of patients drop out before reaching 3 cycles. We

require 20 patients in the treatment arm to be available for analysis; therefore we estimate that 26 patients need to be recruited to this arm. At the time of the change in the randomisation allocation ratio this meant that 47 patients would need to be recruited in total (26 to the treatment arm and 21 to the control arm).

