## **12.5 Statistical analyses**

A full statistical analysis plan will be developed before the first interim analysis of the trial data.

For the primary endpoint, the proportion (and 90% confidence interval) of patients completing NMES for 30min three times a week will be reported.

For the secondary (intention to treat) analyses, change in leg muscle strength from baseline will be compared between trial arms at 9, 17 and 20 weeks.

Descriptive statistics will then be presented for the following measures at 9, 17 and 20 weeks:

- Change in QoL score from baseline
- Change in body composition from baseline
- Change in nutritional intake from baseline
- Change in fatigue from baseline

Response to chemotherapy at 9 and 12 weeks will be described in each trial arm.

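### The intention-to-treat label on the leg-strength comparison does not fit the withdrawal rule: at every visit, change is seen only in participants who are alive, still in the trial and testable

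*Protocol*

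**What the plan says.** **Analysis.** Section 12.5 reads: "For the secondary (intention to treat) analyses, change in leg muscle strength from baseline will be compared between trial arms", with time points at 9, 17 and 20 weeks.

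**Purpose of the late visit.** Secondary objective iii asks: "What is the rate of recovery or decline in these parameters following cessation of 3–4 cycles of chemotherapy", and whether NMES influences it. The synopsis sets the timing as "17/20 week from start of chemotherapy assessments (3/4 cycles received)", so the week depends on the number of cycles given.

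**Who can be measured.**
- Section 6.1 requires "Life expectancy > 3 months" at entry.
- Section 12.3: "A local audit suggests about 25% of patients drop out before reaching 3 cycles".
- Section 10.2 lists death or disability from progression among the events exempt from immediate reporting, so deaths on study are expected.
- Section 11.3 withdraws from the trial participants who stop chemotherapy after 1 or 2 cycles, cannot tolerate the electrodes or NMES, or develop a complication that rules NMES out. After withdrawal there are no further study procedures and no new personal data.

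**What points the other way.** Section 11.3 also asks centres to encourage participants who leave trial treatment to stay in follow-up. Section 15.1 keeps participants given alternative treatment in follow-up and analyses them as allocated.

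**The concern.** Intention to treat promises a comparison of the groups as randomised. A change from baseline at a visit exists only for someone who attends and can be tested. A participant who has died has no change score. One withdrawn under Section 11.3 before week 9 has no strength value after baseline. Those missing are likely to be the frailer participants, so the loss is related to the outcome.

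Two results are exposed. The rate of recovery or decline within an arm would be read as that of patients treated for NSCLC, when it is that of the fitter remainder. The contrast between arms would be read as protected by randomisation, when it compares two selected groups. The trial is meant to inform whether a phase III trial is justified, so the wording of these results matters even though they are secondary.

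**Working it through.** **1. The plan's own retention figure.** Section 12.3 needs 20 analysable patients and allows for 25% loss: 20 / 0.75 = 26.7, which rounds up to 27; the plan states 26. The 25% is thus reproduced to within one patient, and it is the only retention figure given. Nothing is stated for weeks 17/20.

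**2. Loss before week 9.** Applying 25% to both arms: NMES 26 × 0.75 = 19.5; control 21 × 0.75 = 15.75; total 47 × 0.75 = 35.25. Under Section 11.3 those who stop after 1 or 2 cycles give no week-9 value, so the problem starts at week 9.

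**3. Further loss by the follow-up visit.** The protocol gives no survival figure. *Assumption:* exponential survival, median M of 6 to 12 months (26.1 to 52.2 weeks), applied after week 9 to the 75% retained. Fraction measurable at week t = 0.75 × 2^(−(t − 9)/M), with M in weeks.

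| Visit | M = 6 months | M = 12 months |
|---|---|---|
| Week 17 | 0.75 × 0.81 = 61% (28.5 of 47) | 0.75 × 0.90 = 67% (31.7 of 47) |
| Week 20 | 0.75 × 0.75 = 56% (26.3 of 47) | 0.75 × 0.86 = 65% (30.5 of 47) |

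**4. Shift of the mean change within an arm.** *Assumption:* strength change and a latent tendency to remain measurable are bivariate normal with correlation ρ of 0.2 to 0.5, and the top fraction q is measured. Shift = ρ × φ(c)/q SD, where c = Φ⁻¹(1 − q).
- q = 0.75: φ(c)/q = 0.318/0.75 = 0.424; shift 0.08 to 0.21 SD.
- q = 0.60: φ(c)/q = 0.386/0.60 = 0.644; shift 0.13 to 0.32 SD.

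The shift is upward with no true recovery. The protocol gives no SD for strength change, so it cannot be put in kg.

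**5. Shift of the NMES minus control difference.** This is the difference of two such terms (φ(c)/q = 0.570 at q = 0.65).
- 75% retained in each arm: 0.
- NMES 65%, control 75%: ρ × (0.570 − 0.424) = +0.03 to +0.07 SD.
- NMES 75%, control 65%: −0.03 to −0.07 SD.

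The sign follows whichever arm loses more. Withdrawal for NMES intolerance can in practice act in one arm only, so unequal loss is plausible, but the documents do not say how large it is or which arm loses more overall.

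**6. Weeks 17 and 20.** 9 + 8 = 17 and 12 + 8 = 20: this is one visit, 8 weeks after the end-of-treatment time point, dated by cycles received. Cycles received is settled after randomisation. A comparison at week 17 alone sets 3-cycle recipients against 3-cycle recipients, and week 20 does the same for 4 cycles. Neither covers a randomised arm.

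**The case against.** **Intention to treat may only mean analysed as allocated.** Section 15.1 uses it in that sense, and missing outcomes do not by themselves make the label false. Section 12.5 names no model; a repeated-measures analysis could use the week-9 values of those lost later. This stands in part: allocation is respected and complete-case analysis is not written down. But those withdrawn before week 9 contribute no change at any visit, and no model gives a strength value to someone who has died.

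**Deaths and missing data belong in the statistical analysis plan.** That plan is not shown, so the absence of such rules, or of counts by arm, is no finding. The finding is what the protocol does fix: the outcome, the visits, the label and a withdrawal rule that stops data collection.

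**Stronger readings that do not hold.**
- A reader might infer that the entry criterion is the fault, because 3 months is about 13.0 weeks and the visit falls 4 to 7 weeks later. The criterion is a minimum, not an expected survival, and contradicts nothing.
- A reader might take 3 months as the cohort's median, giving deaths of 1 − 2^(−17/13.04) = 59% by week 17 and 65% by week 20. That describes a patient at the boundary.
- A reader might infer that only the late visit is affected. Step 2 shows that week 9 is affected too.

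**Conclusion.** The point holds in a limited form. The label in Section 12.5 and the no-further-data rule in Section 11.3 do not fit together at any visit, and Section 11.3 also sits badly with its own request to keep participants in follow-up and with Section 15.1.

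For objective iii, the recovery seen within an arm is likely to be too favourable by about 0.1 to 0.3 SD. This rests on 60% to 75% being measured and a correlation of 0.2 to 0.5; only the 25% early loss comes from the protocol.

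It would be tempting to add that the NMES effect itself is flattered. The documents do not support that: the between-arm shift is zero with equal retention and changes sign with the arm that loses more. This is a secondary result. Adherence, the primary endpoint, is analysed within the NMES arm during chemotherapy and is untouched.

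**What to change.** 1. Reconcile Section 11.3 (no data after withdrawal, against its own request for continued follow-up) with the label in Section 12.5 and the analyse-as-allocated statement in Section 15.1.
2. Unless data are collected after withdrawal, describe both the 9-week and the 17/20-week contrasts as among participants alive and assessed, by allocated arm. Word the answer to objective iii as recovery or decline in those participants.
3. Treat weeks 17 and 20 as one follow-up visit.
4. As a supplementary analysis, compare the arms at that visit by ranks, with death before the visit lowest and change in strength above it. Use only categories the trial records: reasons for withdrawal are optional, and vital status after withdrawal may be unknown.

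Eligibility stays as it is. The cost of items 2 to 4 is a paragraph of wording and one extra test. The rank result is a composite of death and strength, not expressed in strength units, so it supports the main contrast and does not replace it. Choosing to collect data after withdrawal would cost more: a protocol amendment and the follow-up visits themselves.
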